##### Donor management and contingency plan

2.4.1.2

Donor Consistency: To minimize inter-donor variability as a confounding factor, all participants will receive FMT material from a single, qualified primary donor.Contingency Plan: To prevent study interruption, a backup donor will be fully screened and qualified at the start of the trial. This backup donor will be activated only if the primary donor becomes unavailable for any reason.

##### Ongoing donor monitoring

2.4.1.3

A qualified donor must undergo regular re-evaluation. A screening questionnaire is completed before each donation to identify any interval changes in health or lifestyle. Full serological and stool testing panels are repeated every 8–12 weeks for donors providing samples over an extended period.

#### Recruitment of 30 ASD children

2.4.2

Thirty children aged 2–12 years with moderate-to-severe ASD (CARS score ≥36), diagnosed by [name] (Deputy Chief Physician, Child Health Department, Shenzhen Children's Hospital) according to DSM-5 criteria, will be enrolled after meeting inclusion/exclusion criteria. Participants will be recruited from the patient population of the Child Health Department and the International Medical Center at Shenzhen Children's Hospital.

#### FMT fecal sample preparation

2.4.3

##### Donor fecal collection

2.4.3.1

Fresh donor stool is collected and immediately transported in anaerobic bags to the FMT processing laboratory.

##### Standardized FMT preparation protocol

2.4.3.2

###### Facility

2.4.3.2.1

FMT preparation is conducted in a dedicated laboratory at Shenzhen Children's Hospital.

###### Protocol

2.4.3.2.2

1.Reagents and Consumables:
•2.0 mL threaded centrifuge tubes (Axygen: MCT-200-C), 15 mL centrifuge tubes (Corning: 430791).•150 mL sterile FMT storage bottles (SPL: 56125).•0.9% saline (degassed), 80% glycerol (degassed).•Disposable sterile homogenization bags, 25 mL pipettes, 50 mL centrifuge tubes, sterile tongue depressors, spreaders.•GAM agar plates, reagent racks.•Ice packs, anaerobic containers, cryostorage boxes.

*Note*: All consumables must be sterile; alternative brands are permitted if specified items are unavailable.
2.Equipment:
Biological safety cabinet.Electronic balance.Stomacher homogenizer.−80 °C freezer.Pipettes.3.Microbial Suspension Preparation:
**Step 1**: Fresh stool is visually assessed using the Figure 2 Bristol Stool Form Scale (BSFS, type 3–5 are acceptable; type 1, 2, 6, or 7 result in sample rejection). If transportation compromises visual assessment, donor-provided Bristol scores are used.**Step 2**: Stool is weighed, mixed with 0.9% saline at a 1:3 ratio (e.g., 100 g stool + 300 mL saline), and homogenized for 5 min. Adjustments are made for samples <100 g.**Step 3**: The homogenate is filtered through a membrane-equipped bag using a stomacher (2 min).**Step 4**: Filtrate is transferred to sterile bottles, and glycerol is added to a final concentration of 10% (e.g., 87.5 mL filtrate + 12.5 mL 80% glycerol per 100 mL).**Step 5**: Bottles are labeled with donor ID and preparation time.**Step 6**: Suspensions are stored at −80 °C (stable for ≤6 months) or −20 °C (use within 1–4 weeks). Thaw at room temperature (<6 h) or in a water bath (≤37 °C) before administration.**Step 7**: A “Donor Sample Processing Record” is completed.4.Residual Sample Handling:
Remaining filtrate is aliquoted into 2 mL/15 mL centrifuge tubes with 10% glycerol and stored at −80 °C for quality control and post-treatment analysis.1 mL aliquots of saline and glycerol from the same batch are archived in 2.0 mL tubes.

**Figure 2 F2:**
[figure not shown]
Bristol stool form scale. The figure illustrates the seven types of stool consistency. Adapted from Lewis and Heaton (56).

###### Sample Storage

2.4.3.2.3

All samples are stored long-term in −80 °C freezers at Shenzhen Children's Hospital.

##### Quality control criteria

2.4.3.3

1.**Routine Stool Examination**: Random samples are tested for pathogens and cell counts.2.**Pathogen Detection**: Negative results required for bacterial, parasitic, and viral pathogens; multidrug-resistant genes (e.g., ESBL, carbapenemase) must be absent.3.**Viability Standards**: ≥80% bacterial viability; ≥5 × 10^8^ viable cells/mL.4.**Microbial Consistency**:
Uniform microbial composition within the same donor and batch.No statistically significant differences in microbiota between batches from the same donor within 6 months.5.**Labeling**: Each bottle must be independently packaged and labeled.

#### FMT administration protocol

2.4.4

##### Pre-FMT preparation

2.4.4.1

Patients will begin a semi-liquid diet one day prior to the first FMT administration. Prior to the FMT procedure, all participants will undergo bowel preparation with polyethylene glycol (PEG) lavage to cleanse the intestinal tract, which is consistent with our clinical practice. Given that the FMT is delivered directly to the jejunum, the use of proton-pump inhibitors (PPIs) or other acid suppressants is not planned for this protocol.

##### Nasojejunal tube placement, sedation, and risk management

2.4.4.2

Administration of FMT via the upper GI tract carries specific procedural considerations and risks that must be carefully managed in a pediatric population.
Procedure: The nasojejunal tube will be placed by an experienced pediatric gastroenterologist under the direct visualization of a video endoscope, confirming that the distal tip is correctly positioned in the jejunum past the ligament of Treitz.Sedation: Recognizing that NJ tube placement can cause significant discomfort, anxiety, and requires patient cooperation, the procedure will be performed with appropriate sedation. Each child will undergo a pre-procedural assessment by a pediatric anesthesiologist to determine the optimal, individualized sedation plan. This plan may range from moderate (“conscious”) sedation to general anesthesia, depending on the child's age, anxiety level, and clinical condition, in accordance with the American Academy of Pediatrics guidelines for procedural sedation.Risk Disclosure and Management: The informed consent process will explicitly detail the specific risks associated with upper GI tract administration and NJ tube placement. These risks include, but are not limited to: discomfort or pain during tube placement, risk of aspiration of gastric or fecal contents, potential for mucosal injury or nosebleed, tube dislodgement (e.g., due to coughing or vomiting), and the risks inherent to the sedation or anesthesia itself. Patients will be monitored closely by trained clinical staff during and after the procedure for any adverse events.

##### FMT infusion and schedule

2.4.4.3

Once the NJ tube is confirmed to be in the correct position, patients will be positioned supine. The thawed fecal suspension (dose: 5 mL/kg) will be infused through the tube, followed by a 20 mL saline flush to clear the tube. After the infusion, patients will remain in a supine position for at least 30 min and will be required to fast for 2 h. This procedure will be repeated three times over a 5-day period (i.e., on Day 1, Day 3, and Day 5).

#### Control of confounding variables

2.4.5

To minimize known confounding factors that can influence the gut microbiota, legal guardians will be instructed to maintain the child's typical diet and to avoid introducing major dietary changes (e.g., starting a gluten-free/casein-free diet) during the study period. A baseline 3-day dietary log will be collected. All concomitant medications and the use of supplements will be recorded at each study visit. While household environment cannot be controlled, data on significant dietary patterns and concomitant medications will be collected and considered as potential covariates in exploratory statistical models.

### Outcome measures

2.5

The schedule for all assessments is detailed in Table 1.

**Table 1 T1:** Visit schedule.

Time Window	Within 1 month pre-FMT (Baseline)	FMT treatment period*	1 week post-FMT	2 weeks post-FMT	3 weeks post-FMT	4 weeks post-FMT (±3 days)	5 weeks post-FMT (±3 days)	6 weeks post-FMT (±3 days)***	3 months post-FMT (±3 days)	6 months post-FMT (±3 days)	9 months post-FMT (±3 days)	12 months post-FMT (±3 days)***
Informed Consent	√											
General Data Collection	√	√										
Medical History Collection	√											
Vital Signs, Height, Weight	√	√	√	√	√	√	√	√	√	√	√	√
Inclusion/Exclusion Criteria	√											
Lab Tests**	√	√						√				√
Adverse Event Documentation		√	√	√	√	√	√	√	√	√	√	√
GSRS, DSR	√	√	√	√	√	√	√	√	√	√	√	√
CARS, SRS, ABC	√								√	√	√	√
Recipient Fecal Collection	√	√	√	√		√			√	√	√	√
Donor Fecal Collection	√											

* FMT treatment period: Includes 3 FMT administrations on Day 1, Day 3, and Day 5.

** Lab tests: Baseline tests include routine blood, urine, and stool tests, liver function (ALT, AST), renal function (BUN, Creatinine), coagulation profile, and ECG. Follow-up labs at 6 and 12 months will monitor long-term safety, including: (1) Immune/Inflammatory parameters (CBC with differential, hs-CRP, ESR) and (2) Metabolic parameters (Fasting Glucose, HbA1c, Fasting Lipid Profile, Liver Function Panel, Renal Function Panel).

*** Long-term safety & efficacy follow-ups will specifically monitor long-term safety, including immune, metabolic, and neurodevelopmental parameters.

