#### Primary objective

2.1.1

To investigate the clinical efficacy and safety of FMT in children with ASD.

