a.Neurodevelopmental Parameters: Assessment for any new onset or significant worsening of neurological or psychiatric symptoms using the standardized scales (CARS, SRS, ABC) and clinical evaluation.b.Immune and Inflammatory Parameters: Monitoring for new onset of allergic, atopic, or autoimmune symptoms. Laboratory tests at 6 and 12 months will include Complete Blood Count (CBC) with differential, high-sensitivity C-reactive protein (hs-CRP), and Erythrocyte Sedimentation Rate (ESR).c.Metabolic Parameters: Laboratory tests at 6 and 12 months will include Fasting Blood Glucose, Glycated Hemoglobin (HbA1c), a Fasting Lipid Profile, a Liver Function Panel (e.g., ALT, AST, ALP, Total Bilirubin), and a Renal Function Panel (e.g., BUN, Creatinine) to monitor for metabolic disturbances.d.GI Status: Continued monitoring of GI symptoms via GSRS and DSR.5.Data and Safety Monitoring Board (DSMB): Given the interventional nature of the study and the vulnerable pediatric population, an independent DSMB will be established. The DSMB will be composed of at least three independent experts (e.g., a pediatric gastroenterologist, a child psychiatrist, and a biostatistician) not affiliated with the study. The DSMB will convene to review cumulative safety data after the first 10 participants have completed the 6-week follow-up, and thereafter as needed, to protect participant safety and ensure study integrity.

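### Five long-term safety tests (hs-CRP, ESR, fasting glucose, HbA1c, fasting lipids), and less certainly ALP and bilirubin, have no listed pre-FMT value in this single-arm trial

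*Protocol article*

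**What the plan says.** The double-asterisk footnote to Table 1 (section 2.5, Outcome measures) sets out two laboratory panels. For the pre-treatment visit it says: "Baseline tests include routine blood, urine, and stool tests, liver function (ALT, AST), renal function (BUN, Creatinine), coagulation profile, and ECG". For later visits it says: "Follow-up labs at 6 and 12 months will monitor long-term safety". It then gives two groups: "Immune/Inflammatory parameters (CBC with differential, hs-CRP, ESR") and "Metabolic parameters (Fasting Glucose, HbA1c, Fasting Lipid Profile, Liver Function Panel, Renal Function Panel").

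Section 2.6 (Safety assessment, item 4) repeats the later panel with the same timing. For the metabolic group: "Laboratory tests at 6 and 12 months will include Fasting Blood Glucose, Glycated Hemoglobin (HbA1c), a Fasting Lipid Profile". For the immune group it names a blood count with differential and "high-sensitivity C-reactive protein (hs-CRP), and Erythrocyte Sedimentation Rate (ESR"). It expands the liver entry to "a Liver Function Panel (e.g., ALT, AST, ALP, Total Bilirubin"), so ALP and bilirubin enter the plan only as examples.

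The primary objective (section 2.1.1) is "To investigate the clinical efficacy and safety of FMT in children with ASD". Section 2.2 describes one open-label arm at one centre.

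**The concern.** With no concurrent control, the only internal comparator for a child's laboratory result is that child's own value before the first infusion. For the tests that carry most of the long-term immune and metabolic monitoring, the plan lists no such value.

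This matters for three reasons.

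- **Pre-existing abnormality is plausible.** The inclusion criteria admit children on stable psychopharmacological medication, and the Introduction names metabolic disturbance as an adverse effect of such drugs. A raised glucose or lipid value at follow-up may have been there before FMT.
- **Causality has to be graded.** Section 2.6 requires the principal investigator to classify the relationship of every adverse event to FMT. For these tests there would be no earlier value to consult.
- **The loss is permanent.** A pre-FMT value cannot be obtained once the first infusion has been given, and the article mentions no stored recipient blood.

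**Working it through.** The plan gives no figure on this point. Its one computed design figure, the CARS sample size in section 2.8, is unaffected. The check is a comparison of the two lists, followed by a simple illustration.

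**Step 1: the lists side by side** (Table 1 footnote and section 2.6, item 4).

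| Follow-up test | Listed before FMT? |
|---|---|
| Blood count with differential | Yes, as routine blood |
| ALT | Yes |
| AST | Yes |
| BUN | Yes |
| Creatinine | Yes |
| hs-CRP | No |
| ESR | No |
| Fasting glucose | No |
| HbA1c | No |
| Fasting lipid profile | No |
| ALP (example only) | No |
| Total bilirubin (example only) | No |

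**Step 2: the count.** Twelve follow-up tests are named, five have a listed baseline, and 12 − 5 = 7 do not (7/12 = 58%). Leaving out ALP and bilirubin, 5 of 10 do not. Counting the footnote's own eight entries (three immune, five metabolic), five have no baseline at all and the liver panel is only partly covered.

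**Step 3: other places a baseline might be found.**

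- Section 2.4.1.1 includes a metabolic panel, lipids and hs-CRP, but these are for donor screening.
- Table 1 ticks laboratory tests in the FMT treatment period. It does not say which tests are done or whether blood is drawn before the Day 1 infusion.
- No other section schedules the five firm tests for recipients before FMT.

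**Step 4: timing.** Table 1 ticks laboratory tests at baseline, the treatment period, 6 weeks and 12 months, with no tick at 6 months. The footnote and section 2.6 say 6 and 12 months. The two conflict, but on either reading these tests are first listed after FMT.

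**Step 5: illustration.** The documents give no abnormality rate. Assume that a proportion p of results per test lies outside the reference range whatever FMT does, with p from 2.5% to 10%, and count the lipid profile as one test. The expected number of such results per visit is tests × children × p. Section 2.8 gives 30 enrolled and about 20% dropout, so 30 × 0.80 = 24 children.

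| Tests | Children | p = 2.5% | p = 10% |
|---|---|---|---|
| 7 | 24 | 4.2 | 16.8 |
| 7 | 30 | 5.25 | 21 |
| 5 (without ALP, bilirubin) | 24 | 3 | 12 |
| 5 (without ALP, bilirubin) | 30 | 3.75 | 15 |

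These are expected counts of results, so they do not need independence between tests. The number of children affected would depend on how far the tests are correlated.

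**The case against.** The strongest reply is that the text does not show the tests are omitted. The footnote says what the baseline tests include, which need not be a complete list. The treatment-period tick is undefined, and the source is an article that condenses a fuller protocol. This stands as a limit on wording. A reader might infer that these values are never taken before FMT, but the document supports only that none is listed. It does not remove the point, because the article does not leave the panels to another document. It sets out both, test by test, in one footnote, and they differ. A site following the text would have no instruction to draw the missing tests.

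Second, ALP and bilirubin rest on an example list, so the case for them is weaker. This is accepted; the other five tests do not depend on them.

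Third, a reader might infer that nothing can be said about change in these tests. That goes too far. Follow-up draws can be compared with each other and with reference ranges. What is lost is change from before FMT.

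Fourth, these tests are supplementary. The primary outcomes are GSRS and CARS, and safety also rests on adverse event recording with CTCAE grading, causality assessment and an independent monitoring board. The trial calls itself exploratory, and section 2.7.1 names no test of laboratory values. All true: no primary estimate or sample size changes. But safety is in the primary objective, and section 2.6 gives these tests a specific long-term safety purpose.

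**Conclusion.** The point holds in a limited form. For hs-CRP, ESR, fasting glucose, HbA1c and the fasting lipid profile, and less certainly for ALP and total bilirubin, the plan as written provides no pre-FMT value. With a single arm, abnormalities that pre-date FMT cannot then be told apart from new ones, and change from before FMT cannot be estimated.

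The size is illustrative and rests on an assumed out-of-range rate of 2.5% to 10% per test: about 4 to 17 unclassifiable results per visit over seven tests in 24 children, or 5 to 21 in 30.

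It would be wrong to infer that a baseline would let abnormalities be attributed to FMT. In an uncontrolled study with 12 months of follow-up, it would separate pre-existing from new findings but would not establish cause.

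**What to change.** - **Match the panels.** In the Table 1 footnote and section 2.6, add hs-CRP, ESR, fasting glucose, HbA1c, fasting lipid profile, ALP and total bilirubin to the baseline laboratory tests already scheduled before the first FMT. State that this sample is taken fasting, which the article does not now say. If the tests are already being done, say so.
- **State the reporting.** Give paired change and shift from baseline (for example, normal to abnormal) for each test.
- **Children already treated without a baseline.** Report their values against reference ranges only, and limit the safety conclusion accordingly.
- **Reconcile the schedule.** Table 1 (6 weeks and 12 months) and the text (6 and 12 months) must agree. State also what the treatment-period laboratory tick covers and whether that sample precedes the first infusion.

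The cost is a few extra routine assays, a fasting requirement at baseline and a short amendment. Because the baseline laboratory visit is already in the schedule, no new visit should be needed, provided that sample can be taken fasting.

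### Table 1 places the follow-up safety labs at 6 weeks and 12 months, its own footnote and Section 2.6 at 6 and 12 months; five followed markers are not listed at baseline

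*Protocol article*

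**What the plan says.** Section 2.5 refers the reader to Table 1 for the timing of every assessment. The Lab Tests row has four ticks: baseline, the FMT treatment period, 6 weeks and 12 months. A triple-asterisk mark is attached to two column headers, "6 weeks post-FMT (±3 days") and the 12-month visit. The matching footnote reads "Long-term safety & efficacy follow-ups will specifically monitor long-term safety, including immune, metabolic, and neurodevelopmental parameters".

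The double-asterisk footnote, attached to the Lab Tests row itself, gives a different timing: "Follow-up labs at 6 and 12 months will monitor long-term safety". Section 2.6 agrees with that footnote twice. Item 4b, on immune and inflammatory markers, says "Laboratory tests at 6 and 12 months will include Complete Blood Count (CBC) with differential, high-sensitivity C-reactive protein (hs-CRP), and Erythrocyte Sedimentation Rate (ESR"). Item 4c, on metabolic markers, says "Laboratory tests at 6 and 12 months will include Fasting Blood Glucose, Glycated Hemoglobin (HbA1c), a Fasting Lipid Profile, a Liver Function Panel", followed by a renal panel.

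On content before treatment, the double-asterisk footnote says "Baseline tests include routine blood, urine, and stool tests, liver function (ALT, AST), renal function (BUN, Creatinine), coagulation profile, and ECG". What is drawn during the treatment period is not stated.

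Section 2.6, item 5, has the DSMB "review cumulative safety data after the first 10 participants have completed the 6-week follow-up", with later meetings as needed.

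**The concern.** There are two problems, and the first is the firmer.

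**Timing.** The visit table and the safety text name different visits for the first long-term safety bloods. Staff who work from the table have no instruction to draw blood at 6 months; staff who work from the text do. Safety is part of the primary objective (Section 2.1.1) and the participants are children aged 2–12 years, so it matters which visit yields these data.

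**Baseline.** Several markers named for long-term monitoring do not appear among the baseline tests. The trial has one arm and, as the Discussion notes, no healthy controls. Without a pre-FMT value, a raised HbA1c or hs-CRP after FMT could reflect the intervention or could have been present already. A baseline sample that was not taken cannot be recovered after FMT.

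**Working it through.** The plan gives no numerical result on this point to reproduce. The check consists of mapping the table's cells to its columns and comparing lists.

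**1. Is the table read correctly?** Table 1 has 12 visit columns. The ticks fall as follows:

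| Row | Ticked columns | Visits |
|---|---|---|
| Lab Tests | 1, 2, 8, 12 | baseline, FMT period, 6 weeks, 12 months |
| CARS, SRS, ABC | 1, 9, 10, 11, 12 | baseline, 3, 6, 9, 12 months |

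The second row, read in the same way, matches the timeframes for these scales in Sections 2.5.1 and 2.5.2, so the columns are aligned. The Lab Tests row has its full number of cells, and the triple-asterisk mark also sits on the 6-week header. A shifted cell from text extraction is therefore an unlikely explanation.

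**2. The timing statements side by side.**

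| Place | First long-term lab visit | Second |
|---|---|---|
| Table 1, Lab Tests ticks | 6 weeks | 12 months |
| Table 1, triple-asterisk headers | 6 weeks | 12 months |
| Table 1, double-asterisk footnote | 6 months | 12 months |
| Section 2.6, item 4b | 6 months | 12 months |
| Section 2.6, item 4c | 6 months | 12 months |

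Two features of the table point to 6 weeks and three statements point to 6 months. One visit cannot serve both. With the table's window of 3 days either side, and taking a month as 30 days (an assumption), 6 weeks is day 42 ± 3 = days 39 to 45, and 6 months is day 180 ± 3 = days 177 to 183.

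Following the table alone, the number of children with a scheduled 6-month lab draw is 0 of 30.

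**3. Baseline list against follow-up list.** The follow-up tests and panels number eight:

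| Follow-up test or panel | Listed at baseline? |
|---|---|
| CBC with differential | yes, if the routine blood test covers it (assumption) |
| hs-CRP | no |
| ESR | no |
| Fasting glucose | no |
| HbA1c | no |
| Fasting lipid profile | no |
| Liver panel | in part (ALT, AST) |
| Renal panel | yes (BUN, creatinine) |

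So 5 of 8 have no listed baseline. Splitting the liver panel into ALT, AST, ALP and total bilirubin and the renal panel into BUN and creatinine gives 6 + 4 + 2 = 12 analytes, of which 5 + 2 = 7 are not listed at baseline. The two extra ones, ALP and bilirubin, are given in Section 2.6 only as examples, so the count of five is the safer one.

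**The case against.** The timing conflict itself is hard to dispute. The objections concern how far it reaches, and most of them stand.

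- **Change from baseline.** A reader might infer that change in these markers cannot be estimated for any of the 30 children. The documents do not go that far. The baseline sentence says what the tests include, which is not an exhaustive list; the content of the treatment-period draw is not stated; and a journal article may leave the full panel to the complete protocol. What can be said is that the markers are not listed before FMT. Nor does the article specify a change-from-baseline analysis of laboratory values, and reference ranges remain available. The loss would be in attributing an abnormality, not in detecting one.
- **The DSMB.** A reader might infer that, under the text, none of the first 10 children would have 6-week labs when the DSMB meets. The text states what is drawn at 6 and 12 months; its silence on 6 weeks does not exclude a draw then. The review also does not rest on labs alone: adverse events, vital signs, GSRS and DSR are all scheduled at 6 weeks, and labs are ticked in the treatment period.
- **Neurodevelopmental monitoring at 6 weeks.** The triple-asterisk footnote includes it, and CARS, SRS and ABC are not ticked there. A reader might call this a further contradiction, but item 4a of Section 2.6 also allows clinical evaluation. The 6-week mark and the 6-week lab tick may share one slip.
- **Two lists in one article.** It can be said that analyte detail belongs in a fuller document. That carries less weight here, because the article itself sets out both lists by name and they differ.

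**Conclusion.** The concern holds in two parts of unequal strength.

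The timing contradiction is certain on the face of the document. Nothing in the article shows which visit is intended, and this review takes no side. It decides whether any child has safety bloods at 6 months, so it is more than clerical.

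The baseline mismatch is real as a difference between two stated lists, covering 5 of 8 follow-up tests or panels. Its consequence is conditional: if the markers are not in fact drawn before FMT, a later abnormality can be compared only with reference ranges. The count assumes that the baseline routine blood test covers the CBC with differential; if it does not, the count is 6 of 8.

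Neither part touches the CARS or GSRS analyses or the sample size.

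**What to change.** 1. Reconcile the Lab Tests ticks and the triple-asterisk header marks in Table 1, its double- and triple-asterisk footnotes, and items 4b and 4c of Section 2.6, so that all name the same visits.
2. With the schedule settled, confirm which laboratory results will be available at the DSMB review that follows the 6-week visit of the first 10 participants.
3. Reconcile the baseline and follow-up analyte lists, so that any marker meant to show change after FMT also has a listed pre-FMT value. If these markers are already drawn before treatment, it is enough to say so.

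Items 1 and 2 cost only a correction of the text. Item 3 costs at most a few added assays at the baseline draw that Table 1 already schedules. Glucose and lipids are specified as fasting at follow-up and the baseline draw is not described as fasting, so that draw may have to be arranged accordingly. Item 3 has to be settled before a child's first FMT to be of use for that child.
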